### Participants and eligibility criteria

Competent doctors will strictly screen qualified subjects according to inclusion and exclusion criteria.

Seventy patients with lung cancer, an American Society of Anesthesiologists physical status I–II, an age of 30–70 years, and a VAS score ≥ 7 who are selected for VATS lobectomy will be recruited for this clinical study. They will also be required to be able to communicate well and understand how to score their pain level. All eligible participants who meet the study inclusion criteria will be identified through the Division of Thoracic Surgery. The study exclusion criteria are coagulation disorders; neuropathy; infections at the site of acupotomy; obesity (body mass index, BMI > 30 kg/m^2^); clinically significant neurological, cardiovascular, renal, and hepatic diseases; an inability to remove the tracheal catheter or to correctly use the PCA pump after surgery; psychiatric illnesses that would interfere with the perception and assessment of pain; and pain-killer use within a week before surgery.

We will have dedicated researchers to screen existing institutional registry records and databases and to work closely with the thoracic surgeons to identify qualified participants. Once eligibility is established, the research staff will contact eligible participants or their families and explain the purpose and significance of this study, provide full explanations to eliminate participants’ doubts, and ascertain interest in enrolment. If a participant agrees to enrol, informed consent will be obtained. Participants will undergo baseline assessments following informed consent provision. A CONSORT diagram of participant recruitment is shown in Table 1.

**Table 1 Tab1:** Trial process chart

Items	Before enrollment -2-1 (weeks)	PACU	Postoperative 1 h	Postoperative 2 h	Postoperative 4 h	Postoperative 8 h	Postoperative 12 h	Postoperative 24 h	Postoperative 48 h	Postoperative 72 h
Inclusion criteria	×									
Exclusion criteria	×									
Informed consent	×									
Randomization and allocation	×									
**Pain scores** (VAS)		×	×	×	×	×	×	×	×	×
Postoperative requirements for rescue analgesia		×	×	×	×	×	×	×	×	×
LOS		×	×	×	×	×	×	×	×	×
BCS		×	×	×	×	×	×	×	×	×
FAS		×	×	×	×	×	×	×	×	×
Cumulative amount of self-administered analgesics								×	×	×
Adverse events		×	×	×	×	×	×	×	×	×
Patients’ satisfaction								×	×	×

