### Study intervention

#### Interventions, anaesthesia, and patient-controlled analgesia

All patients will be expected to avoid preoperative use of pain medication. After entering the operating room, clinicians will regularly monitor the patients’ blood pressure, electrocardiography, pulse oxygen saturation (SpO_2_), and end-tidal carbon dioxide tension (PETCO_2_).

Then, patients will receive general anaesthesia under a standard protocol. General anaesthesia will be induced with 0.05 mg/kg of midazolam, 2–4 μg/kg of fentanyl, and 2 mg/kg of propofol intravenously. Tracheal intubation will be facilitated with rocuronium bromide 0.6 mg/kg. If necessary, we will repeat intubation. We will use 1–2% sevoflurane to maintain anaesthesia. During the surgery, patients will intravenously receive propofol and remifentanil at doses of 2–2.5 μg/kg and 3–4 μg/kg, respectively. In addition, we will continuously administer cisatracurium besylate to maintain muscle relaxation. The oxygen concentration will be adjusted according to the arterial blood gas value of the partial arterial blood oxygen concentration value. PETCO_2_ will be controlled between 35 and 40 mmHg. A left-sided double-lumen endobronchial tube will be inserted under the premise that the tube size matches the left mainstem bronchial diameter. We will confirm the correct tube position with the help of a stethoscope and flexible fibreoptic bronchoscopy. At 30 min before the end of the operation, we will give the patients 5–10 mg of dezocine intravenously. Patients in the conventional PCA group will be immediately connected to an intravenous self-control analgesia pump containing 2 μg/ml of sufentanil and 8 mg of ondansetron diluted in 100 ml of 0.9% saline after surgery. The initial loading dose will be 2 ml, the background dose will be 2 ml/h, the single PCA dose will be 0.5 ml, and the locking time will be 15 min. Patients will not be treated with other medical analgesics. If special requirements emerge, the study will record the specific medication time, the drug name, each dose, the total dosage, and other information in detail. Patients in the acupotomy combined with PCA group will be treated with acupotomy before PCA treatment.

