### Outcome measures

When patients are transferred to the PACU, vital signs (heart rate, noninvasive blood pressure, respiratory rate, and SpO_2_) will be monitored and recorded every 5 min for at least 30 min. When the patients’ vital signs are stable and they are able to communicate easily, a series of clinical-scale evaluations and analgesia will be evaluated and recorded. The primary outcome measure of this study is the postoperative pain intensity score. Pain scores (VAS) in the PACU and postoperatively at 1, 2, 4, 8, 12, 24, 48, and 72 h at rest and coughing in each group will be assessed. The VAS ranged from 0 = no pain to 10 = unbearable pain. The mean value and standard deviation will be used for descriptive analysis. The primary outcomes of this study were the resting and dynamic pain scores, which were recorded using a VAS. The secondary outcome measures are postoperative requirements for rescue analgesia, the cumulative amount of self-administered analgesics, the level of sedation (LOS), the Bruggemann comfort scale (BCS), and the functional activity score (FAS) concerning adverse effects and patient satisfaction.

The time to the first rescue analgesic use and the cumulative amount of self-administered analgesics in the first 48 and 72 h will be recorded. The BCS, LOS, and FAS will be recorded at 1, 4, 8, 16, 24, 48, and 72 h after surgery. The LOS is recorded on a 5-point scale, with 0 indicating fully awake, 1 indicating drowsy/closed eyes, 2 indicating asleep/easily aroused with light tactile stimulation or a simple verbal command, 3 indicating asleep/arousable only by strong physical stimulation, and 4 indicating unarousable. The BCS is scored as 0, persistent pain; 1, severe pain while deep breathing or coughing; 2, mild pain while deep breathing or coughing; 3, painless while deep breathing; and 4, painless while coughing. The FAS is scored as A, not restricted; B, mild to moderately restricted; and C, severely restricted. Postoperative adverse effects such as nausea, vomiting, hypotension, hypoxemia, cardiac arrhythmia, and the complications from the drugs and technique will be recorded and treated.

Patient satisfaction will be assessed verbally at 24, 48, and 72 h after surgery using a 5-point Likert scale (5 = completely satisfied, 4 = quite satisfied, 3 = slightly dissatisfied, 2 = dissatisfied, 1 = very dissatisfied). The observer who records the postoperative data will also be blinded to the group assignments.

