### Statistical analysis

The statistical analysis will be carried out using SAS (SAS 9.2) statistical software. All allocated subjects with available data will be analysed, i.e. on the basis of the intention-to-treat principle. The continuous variables will be presented as the means ± SDs (standard deviations) or the medians (25th to 75th centiles) and compared using the two-tailed Mann-Whitney test or Student’s *t* test, as appropriate. Categorical variables will be presented as numbers and percentages and analysed by Fisher’s exact test or the chi-squared test. Repeated measurements will be analysed using two-way ANOVA, and Tukey’s test will be used for post hoc testing. All statistical tests will be performed with a bilateral test, and *P* ≤ 0.05 will be considered as statistically significant.

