## Discussion

This prospective randomized control study aims to evaluate the effects of acupotomy combined with PCA (compared to conventional PCA) on postoperative pain, functional recovery, postoperative adverse effects, and patient satisfaction among patients undergoing VATS with poorly controlled postoperative pain. Despite the application of minimally invasive techniques, improved administration of analgesic drugs, and combined use of analgesic drugs, the postoperative pain of some patients after thoracoscopic surgery is not well controlled [22].

As a concept for a multimodal perioperative analgesic regimen, the options for postoperative analgesia must be effective with minimal side effects and aim to decrease the potentially harmful consequences of thoracic surgery on immediate and long-term patient well-being [23, 24]. Moreover, as improving patients’ recovery after surgery and reducing patients’ hospital stay are key aims of fast-track surgery, other pain-relieving strategies must be considered to complement the analgesics currently used [25–27].

PCA is a common analgesic method after thoracoscopic surgery in clinical practice [1, 28], and acupotomy is a traditional Chinese acupuncture treatment focusing on the pain treatment of clinical diseases [29, 30]. The combination of acupotomy and conventional PCA can provide new insights into complicated postoperative pain management and functional rehabilitation of patients after thoracoscopy.

In this study, we will use a combination of patient-reported subjective evaluation scales and objective statistical evaluation indicators of the effect of analgesic use to verify the effect of acupotomy combined with PCA on pain after thoracoscopy, thus increasing the reliability of the research results. In addition, early rehabilitation of postoperative limb function is also an important part of evaluating the effect of surgical treatment. In this study, the FAS scale will be used to evaluate the recovery of upper limb motor function in patients after thoracoscopic surgery. At the same time, we will also focus on evaluating adverse reactions and patient satisfaction. To the best of our knowledge, this will be the first randomized controlled trial to study the effect of a combination of acupotomy and PCA on the management of postoperative pain and functional recovery in this population.

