The major limitation of this protocol is its non-double-blind design. Nevertheless, we have taken some remedial measures to further ensure the quality of the research. For instance, patients will be allocated using a computerized randomization schedule to receive either of two techniques, which may control for selection bias. Moreover, the outcome assessors and statistical analysts will be blind to the intervention, which may control for report bias. Another limitation of this study is that no blank control group was established to exclude the placebo effect. We will consider this issue in the next more rigorous experimental design. This study also lacks long-term follow-up observations and assessments. The 3-day continuous observation period reflects the real-world clinical practice of the observation of acute analgesia after thoracoscopy and is sufficient to confirm the clinical efficacy and safety of acupotomy combined with PCA in the short-term treatment of pain after thoracoscopy.

In conclusion, our results may offer an innovative strategy for improving postoperative pain control that could have a substantial impact on postoperative care and quality of life for patients undergoing VATS.

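### Time to first rescue analgesic has no named test, and the listed tests that fit it, run on observed times, would compare only rescued patients

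*Protocol article*

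**What the plan says.** The Outcome measures section names the need for rescue analgesia as a secondary outcome and then says that "The time to the first rescue analgesic use" will be recorded. In Table 1 the row "Postoperative requirements for rescue analgesia" is marked at every assessment from the PACU to 72 h. The Discussion confirms the window: "The 3-day continuous observation period reflects the real-world clinical practice".

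Under Interventions, anaesthesia, and patient-controlled analgesia, the regimen is PCA alone: "Patients will not be treated with other medical analgesics". Exceptions are logged: "If special requirements emerge, the study will record the specific medication time", along with drug and dose.

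The Statistical analysis section allots tests by type of data. Continuous variables are "compared using the two-tailed Mann-Whitney test" or by Student's t test, whichever suits. Categorical variables go to Fisher's exact or chi-squared tests, and repeated measurements to two-way ANOVA with Tukey's test. No time-to-event method is listed. The analysis set is described in one sentence: "All allocated subjects with available data will be analysed, i.e. on the basis of the intention-to-treat principle". The Discussion counts "objective statistical evaluation indicators of the effect of analgesic use" among the evidence that is meant to support the result.

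**The concern.** A patient who needs no rescue by 72 h has no rescue time. What is known is that the time exceeds 72 h, which is a censored value. Student's t and Mann-Whitney tests run on the recorded times have nowhere to put that patient, so the patient drops out of the comparison.

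The patients left out are those with the best result on this measure, and if acupotomy works there are more of them in its arm. The remaining contrast asks how late rescue came among those who needed it. That is not a randomized comparison, and it discards most of the information about benefit. Participants cannot be blinded and the primary outcome is self-reported pain, so a supporting measure based on drug use deserves an analysis that can show an effect if there is one.

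**Working it through.** **Inputs from the article.** 35 patients per group (Sample size); observation to 72 h (Table 1, Discussion); two-sided tests at 0.05 (Statistical analysis).

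**Assumed, because the article gives no figure.** Control rescue rate by 72 h, p_c, from 40% to 99%; hazard ratio, acupotomy against control, of 0.5, with 0.43 and 0.6 as alternatives; exponential times; no drop-out.

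**The plan's own figure.** The article has none for rescue time. Its VAS effect size reproduces: (3.47 − 2.34)/√((1.39² + 1.21²)/2) = 1.13/1.303 = 0.867. It does not bear on this measure.

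**Step 1: which listed test fits.** One time per patient is neither categorical nor repeated. That leaves Student's t or Mann-Whitney. This is an inference, since the article names no test for the measure.

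**Step 2: who has an observed time.** With hazard λ = −ln(1 − p_c)/72, the acupotomy rescue rate is p_a = 1 − (1 − p_c)^HR. At p_c = 80% and HR 0.5, p_a = 1 − √0.20 = 55%. Expected rescued patients are 35 × 0.80 = 28.0 and 35 × 0.553 = 19.3.

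**Step 3: what is left of the contrast.** Among those rescued by T = 72 h, the mean time is 1/λ − T·e^(−λT)/(1 − e^(−λT)). At p_c = 50% and HR 0.5:
- control: 103.9 − 72 × 0.5/0.5 = 31.9 h
- acupotomy: 207.7 − 72 × 0.7071/0.2929 = 33.9 h

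A halved hazard appears as a 2 h difference, while the rescue rates are 50% and 29%.

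**Step 4: power by simulation.** 3,000 trials per cell, HR 0.5, power in %:

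| Control rescued by 72 h | Acupotomy rescued | Mann-Whitney, rescued only | Mann-Whitney, unrescued tied at 72 h | Log-rank | Fisher, rescued yes/no |
|---|---|---|---|---|---|
| 40% | 23% | 4.6 | 34.1 | 34.7 | 26.3 |
| 60% | 37% | 6.6 | 48.8 | 51.4 | 38.2 |
| 80% | 55% | 12.2 | 61.4 | 66.1 | 50.3 |
| 90% | 68% | 18.7 | 64.6 | 72.1 | 52.0 |
| 95% | 78% | 27.0 | 65.8 | 76.7 | 44.7 |
| 99% | 90% | 48.4 | 68.5 | 79.7 | 9.9 |

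A separate run at 40/60/80/95% gave 4/7/10/28% for rescued only, 36/48/62/69% for Mann-Whitney with ties and 37/50/67/78% for log-rank. The two runs agree to within about 3 points.

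**Step 5: other effects, same six control rates.**
- HR 0.43: rescued only 5/6/13/23/36/60%, log-rank 46/64/82/87/89/92%.
- HR 0.6: rescued only 5/5/9/16/20/32%, log-rank 23/32/42/49/52/55%.

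**Step 6: no effect (HR 1).** Rejection rates were 4.3-5.8% (rescued only), 4.1-5.5% (tied) and 4.6-5.8% (log-rank).

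**The case against.** The strongest reply is that this turns silence into error. The article says only that the time is recorded. It does not say that the time will be tested, which test applies, or that unrescued patients are left out. A patient followed to 72 h without rescue does have data, because Table 1 records the need for rescue at each assessment, and leaving that patient out sits badly with the intention-to-treat principle. A rule for such patients may also sit in an analysis plan that is not shown. This stands in part: the rescued-only comparison is what the listed tests lead to naturally, but it is not something the article prescribes.

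A reader might infer that neither listed test can deal with unrescued patients. That is too strong. With a common 72 h cut-off and complete follow-up, Mann-Whitney is valid if all unrescued patients share the highest rank, and it gives up little against log-rank when control rescue is 80% or less. What is missing is the rule. A t test with 72 h substituted also kept its error rate in simulation (4.5-5.2%), but it compares truncated means.

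A reader might also infer that acupotomy would be made to look worse. That can be constructed: with 80% against 50% rescued and acupotomy preventing mainly late rescues (15% of the earlier half, 60% of the later), the rescued-only Mann-Whitney test is significant in the wrong direction in 17% of trials. Nothing in the article supports that pattern, and the yes/no comparison still finds the benefit in 69% of those trials.

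Finally, patients enter with a VAS score of at least 7, so rescue may be common, and the section restricting other analgesics does not use the word rescue. The share left unrescued is therefore unknown. The gap narrows when nearly everyone is rescued, but at 99% control rescue and HR 0.5 it is still 79.7 − 48.4 = 31 points.

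**Conclusion.** The point holds in limited form and is minor. The article names no test for time to first rescue. The listed tests that fit, run on observed times, would compare only rescued patients and lose most of the power: about 4-28% against 37-78% for log-rank at HR 0.5 with 40-95% of controls rescued. Those figures rest on assumed rescue rates and hazard ratio, exponential times, 35 per arm and no drop-out, and they apply only if unrescued patients are left out.

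A reader might go further and infer false positives or damage to the main result. Neither follows. Rejection under no effect stays near 5%, and the VAS outcome, the sample size and the rescued yes/no comparison do not depend on this choice. One supporting secondary measure is affected.

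**What to change.** Add to the Statistical analysis section: *Time to first rescue analgesic will be analysed in all randomized patients by Kaplan-Meier curves and a two-sided log-rank test, with a Cox hazard ratio and 95% CI. Patients not rescued are censored at 72 h or at withdrawal.*

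Where follow-up is complete, a Mann-Whitney test with unrescued patients tied at the highest rank at 72 h is an acceptable alternative. At HR 0.5 it costs about 1 to 5 points of power against log-rank for control rescue of 40-80%, and about 8 to 11 points at 90-99%. It is not suitable for a patient who withdraws unrescued before 72 h, who would wrongly be given the best rank. A t test or any rescued-only comparison should be ruled out for this measure.

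The cost is a change of wording. No new data are needed, because the time of any extra analgesic is already to be recorded and rescue need is already assessed to 72 h.

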**Methods:**

The study will be a single-centre, parallel group, randomized controlled trial.

Seventy patients with significant pain after thoracoscopic surgery with a visual analogue scale (VAS) score ≥ 7 will be included and randomly distributed into two groups: G1, the acupotomy combined with PCA group; and G2, the conventional PCA group. The primary outcome measure is pain scores at rest and coughing evaluated with the VAS by a blinded observer in the postanaesthesia care unit (PACU) and postoperatively at 1, 2, 4, 8, 12, 24, 48, and 72 h. The secondary outcome measures are postoperative requirements for rescue analgesia, the cumulative amount of self-administered analgesics, the level of sedation (LOS), the Bruggemann comfort scale (BCS), and the functional activity score (FAS) concerning adverse effects and patient satisfaction.

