### Randomization and blinding

In this study, we will use SAS (SAS 9.2) statistical software to create a randomization sequence generated by an independent statistician. The randomization sequence will assign patients on the basis of a 1:1 ratio to either the intervention group (acupotomy combined with PCA group) or the control group (conventional PCA group). The allocation sequence (containing random numbers and allocation and intervention information) will be concealed from the researchers who are responsible for enrolling and assessing participants in sequentially numbered, opaque, sealed, and stapled envelopes. The project manager will evaluate the baseline information of eligible participants and then inform them of the group to which they are assigned. Study personnel involved in recruitment, screening, data collection, and data entry will be blinded to group assignments. Due to the nature of the intervention, blinding the participants is impossible.

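### Satisfaction is a spoken rating from patients who know their arm, which invites courtesy bias that can differ by arm and adds one avoidable chance for the observer to learn the allocation

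*Protocol article*

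**What the plan says.** Patient satisfaction is a secondary outcome. Outcome measures in the protocol article sets both its mode and its times: "Patient satisfaction will be assessed verbally at 24, 48, and 72 h after surgery using a 5-point Likert scale". Table 1 gives the same three times. The next sentence in that section reads "The observer who records the postoperative data will also be blinded to the group assignments".

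Randomization and blinding states that "Due to the nature of the intervention, blinding the participants is impossible". The project manager is to assess baseline information from eligible participants and "then inform them of the group to which they are assigned". The same section also says: "Study personnel involved in recruitment, screening, data collection, and data entry will be blinded to group assignments".

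The Discussion names the lack of double blinding as the major limitation. Among the remedies it offers is that "the outcome assessors and statistical analysts will be blind to the intervention, which may control for report bias".

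**The concern.** Two features of the stated method work against each other. The patient knows the arm, and the patient gives the satisfaction rating aloud to someone from the trial.

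The first consequence concerns the satisfaction comparison itself. People tend to give kinder answers face to face than in private. If that tendency were equal in both arms it would mostly shift the level. Here it need not be equal: the acupotomy group has had an additional procedure performed on them by a senior practitioner, and the control group has not. A polite upward shift in one arm would look like a treatment effect on satisfaction. The Discussion's remedy does not reach this, because the bias arises in the patient's answer, whatever the listener knows.

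The second consequence is smaller. If the person who asks is also the person who rates the patient later, a spoken question about satisfaction is an avoidable occasion for the patient to mention the needling or its absence. Later ratings that involve observer judgement could then be coloured by knowledge of the arm. The clearest example is sedation (LOS), which depends on how easily the patient is roused.

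**Working it through.** The article states no figure on this point, so the check is a reading of the sections side by side plus a count of time points.

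**1. Does the patient know the arm?** Yes. Randomization and blinding says so twice: participants cannot be blinded, and they are told their group.

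**2. Is the answer spoken?** Yes. Outcome measures commits to a verbal assessment. This is a stated method and not a detail left open.

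**3. Who asks?** Not stated. Three things point to the blinded observer: satisfaction is postoperative data, staff who collect data are to be blinded, and the sentence on the blinded observer directly follows the satisfaction item. This is an inference. The courtesy-bias part does not depend on it; the disclosure part does.

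**4. What comes before and after the first question at 24 h?** Inputs: the VAS times in Outcome measures (PACU, 1, 2, 4, 8, 12, 24, 48 and 72 h), each at rest and on coughing.
- Before 24 h: PACU, 1, 2, 4, 8 and 12 h = 6 of 9 assessments, or 6 × 2 = 12 of 9 × 2 = 18 VAS scores.
- At the 24 h visit: 1 of 9 assessments, or 2 of 18 scores. The article gives no order of items within this visit.
- After 24 h: 48 and 72 h = 2 of 9 assessments, or 2 × 2 = 4 of 18 scores.
- LOS, BCS and FAS: Outcome measures lists 1, 4, 8, 16, 24, 48 and 72 h, so 2 of 7 times fall after 24 h. Table 1 lists nine times for these scales, which would make it 2 of 9.

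**5. What other routes to disclosure exist?** Each of the six earlier pain assessments already brings a patient who knows the arm into contact with the observer. Adverse events are recorded from the PACU on (Table 1) and include complications of the technique (Outcome measures). The section on adverse events names discomfort or bruising at the needle site, and Acupotomy treatment has gauze applied there. The satisfaction question adds to these routes; it does not open the first one.

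**6. Which outcomes could a lost observer blind affect?** VAS is the patient's own rating, so the patient's knowledge exposes it from the PACU on, whatever the observer knows. Observer knowledge could add only an influence on prompting and recording. LOS is rated by the observer. BCS is defined by pain on breathing and coughing, which the patient must report. The article does not say who grades FAS.

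**The case against.** The strongest case against the point is that nothing here is contradictory. A verbal rating and a blinded observer can coexist. The patient picks one of five labels, and that choice need not reveal anything. The article does not name the interviewer, does not say that the same person returns at 48 and 72 h, and does not say that the question is about the pain treatment. The order of items within a visit and instructions not to disclose the arm are matters that an article commonly leaves to the full protocol. The acupotomy doctors are kept out of evaluation, so the answer is not meant to go to the person who did the needling. The open design and the lack of a control for placebo effect are both admitted in the Discussion. A card would not remove expectation effects and may be left blank.

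Most of this stands against the disclosure part. A reader might infer that the satisfaction question makes the blinded observer learn the arm and so undermines the 48 and 72 h results. The documents do not support that: the interviewer is inferred, earlier contacts and the recording of technique complications are equally open routes, and no disclosure rate is given or can be derived.

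It does not dispose of the courtesy-bias part. Keeping the treating doctor away reduces the pressure to please but does not remove it, since the answer is still spoken to trial staff. The Discussion's limitations do not mention this bias. The spoken mode is fixed in the text, so this is not a complaint about a missing detail.

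**Conclusion.** The point holds as a minor one. A spoken satisfaction rating from patients who know their arm can carry a courtesy bias that differs between the groups, and assessor blinding offers no protection against it. On the natural but unstated reading that the blinded observer asks, the spoken question is also one more avoidable occasion for disclosure before 2 of the 9 pain assessments, among several occasions that exist already.

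The size of the courtesy bias cannot be worked out from the documents, and no count of unblinded patients is offered because any disclosure rate would be invented. The effect falls mainly on one secondary outcome. The primary VAS comparison is exposed chiefly because unblinded patients rate their own pain, and changing how satisfaction is asked does not alter that.

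**What to change.** In Outcome measures, keep the 24, 48 and 72 h times and the five scale points, and replace the spoken assessment with a self-completed card:

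- At each of the three visits the observer records VAS, LOS, BCS and FAS first.
- The patient then marks the satisfaction card alone and seals it in an envelope. The card carries the participant number and no reference to the treatment.
- The envelope is opened only at data entry.

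Scoring first also keeps the 24 h ratings clear of the satisfaction question.

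The cost is a sentence or two of protocol text, a printed card and an envelope, with no added staff or visits. The downside is that a few cards may be left blank by patients who find writing hard soon after surgery. The change should be described as a less biased way to collect satisfaction and not as restoring the observer's blind, since the other routes to disclosure remain.
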